#### Motivational Messages

The study team also created a library of approximately 200 motivational messages to be delivered between sessions. These will include text-based messages and brief videos created by research staff, adapted from the UCARE4LIFE study [58], and supplemented with the CDC’s #ShesWell: PrEP for Women campaign to promote the uptake of PrEP among women of color. A sample of these messages were provided to phase 1 and phase 2 participants who provided their feedback on the language and acceptability of the messages. The messages are intended to motivate participants to attend their appointments with the nurse practitioner, take PrEP daily as prescribed for those on daily oral PrEP, continue their SUD treatment, speak with the nurse practitioner regarding side effects or questions, and decrease sexual behaviors that may increase their susceptibility to HIV infection.

#### Theater Testing

The investigators invited 5 participants who had completed the qualitative interviews in phase 1 to a theater testing session to provide feedback on the developed intervention, including the motivational messages that had been created. The investigators conducted theater testing from February 19 to February 28, 2024. Participants were compensated US $25 for their time. During the theater test, participants completed a 45-minute sample session, which included elements from the 4 planned sessions of the full intervention. Following the theater test, each participant completed a feedback form with open and closed-ended questions and participated in a 15-minute interview to obtain their reactions to the proposed intervention [59]. The research team used this feedback to tailor the specific content of the sessions further to be more appealing to women engaged in treatment for SUD who have increased susceptibility to acquiring HIV.

### Phase 3: Intervention Pilot Test—Study Design

The investigative team will rigorously pilot test the degree to which the addiction clinic–based behavioral intervention promotes increased PrEP adherence compared with standard linkage to PrEP. The investigative team will randomly assign 60 women to 1 of the 2 conditions. Participants in both the intervention and control groups will continue to receive evidence-based behavioral therapy for SUDs (ie, cognitive behavioral therapy with licensed counselors).

### Participants and Recruitment

The investigators will recruit 60 BlackBlack or Hispanic women to participate in the study. The investigators will invite individuals who are engaged in or initially enrolling in treatment for SUDs at the CNRA. The research assistant will describe the study by informing participants that this is an HIV prevention study focusing on women engaged in treatment for SUD and will not directly impact their regular SUD treatment. Potential participants will be screened over the phone by the research assistant and informed of the purpose of the study. Those meeting inclusion criteria and agreeing to participate will sign an informed consent form and receive a copy. After completing the informed consent process, participants will be randomized to the intervention or control group.

The study team will recruit eligible participants by posting flyers, through word of mouth (through addiction treatment staff referral), and advertising in local print sources (newspapers and magazines). Recruitment and enrollment began in May 2024 and will continue through March 2025.

### Intervention Arm

#### Weekly Counseling Sessions

Participants randomized to the addiction clinic–based behavioral intervention will receive 4 motivational counseling sessions (~30 minutes each) related to HIV prevention, PrEP, and partner communication information delivered by a trained study counselor with expertise in HIV prevention among substance using populations. The study counselor will assist the participant with downloading the Scene app and completing a profile. The incentive scheme and expectations for treatment will be explained at the time of the baseline assessment.

#### In-Clinic PrEP Screening

After completion of the four motivational sessions, the participant will be scheduled for their initial visit with the nurse practitioner in the CNRA, who will conduct a clinical assessment which will include fourth-generation HIV screening (ie, tests that detect both HIV antibodies and p24 antigens), screening for sexually transmitted infections, a basic metabolic panel to include serum creatinine, and hepatitis B and C screening. The nurse practitioner will review laboratory results. If there is no contraindication for PrEP, the participant will be provided a prescription for PrEP. The decision to prescribe daily oral PrEP or long-acting injectable (LAI) PrEP will be based on a collaborative decision-making process between the patient and nurse practitioner, considering clinical appropriateness, patient choice, and medication availability. Participants on daily oral PrEP will be instructed to take the medication daily and to follow up for laboratory tests in 12 weeks while participating in the intervention. Participants enrolled in LAI-PrEP will be provided with a prescription for a 4-week supply of oral cabotegravir per local clinic protocol of prescribing lead-in medication to monitor side effects before initiating LAI-PrEP. Participants are then instructed to follow up with the nurse practitioner in 4 weeks for their first injection while participating in the intervention. All participants who receive a PrEP prescription from the on-site nurse practitioner will meet with the risk reduction specialist, who will assist those without prescription insurance with enrollment for an appropriate patient assistance program to access medication free of charge through the Advancing Access Program or the Health and Human Services ready, set, PrEP program.

#### Medication Adherence Monitoring

Participants will be instructed to provide proof that they are in receipt of the prescribed PrEP medication (video message within the Scene app) and to begin daily video uploads of adherence to medication regimen. Participants who do not fill their PrEP prescription within 2 weeks will be scheduled for a follow-up visit with the nurse practitioner, who will address any concerns and questions related to starting the medication. Participants who are prescribed daily oral PrEP will be asked to upload daily adherence videos (ie, video of the participant taking the medication) for 12 weeks after initiating PrEP.

#### Motivational Messaging

Participants will receive motivational messages through text for the entire 12 weeks to promote medication uptake (for participants who, after the motivational counseling sessions, have not chosen to start PrEP and agree to continue receiving the informational messages) or reminders and motivational messages to support adherence to PrEP (for participants who initiate PrEP). All participants will be given the option of choosing how often they receive the messages and can opt out of messaging at any time through the app.

#### Monetary Incentives

Participants will receive monetary incentives for completing project-related tasks and engaging in desirable health-promoting behaviors. Each participant will receive US $25 for the baseline data collection, US $10 per session for attending 4 weekly motivational counseling sessions, US $25 for the initial nurse visit with laboratory tests, US $10 for providing proof of the initial prescription fill, US $1/day for uploading daily adherence videos during weeks 5-16 (those on LAI-PrEP will receive US $1/day for weeks 4-8 and US $60 for proof of injection for weeks 9-16), US $25 each for data collection at 4-weeks and 1-weeks post baseline, US $25 for the 90-day follow-up visit with the nurse practitioner, and US $50 for completing the follow-up data collection at week 16 (US $309 possible for the entire intervention).

#### Control Arm

Participants randomized to the control arm will receive standard of care PrEP information along with a referral and a scheduled appointment with Allies in Hope. Transportation assistance for appointment attendance will be provided. In this agency, if there is no contraindication for PrEP, the participant will be provided a prescription for daily oral PrEP or long-acting injectable PrEP and follow up with the community-based partner per normal procedures at that facility. Allies in Hope will provide the research team with information regarding appointment attendance and whether a prescription was provided to the participant, with consent from the participant. Participants in standard treatment will continue to receive their regular SUD treatment services.

#### Monetary Incentives

Participants in the control arm will receive the same incentives, except for the weekly session amounts, for a possible total of US $269 for the entire study. Standard treatment participants will not have access to the Scene Health app and will be asked to respond to a daily yes or no question regarding medication adherence through REDCap (Research Electronic Data Capture; Vanderbilt University) with the same US $1/response incentive.

### Data Collection

Participants in both arms will complete baseline surveys and follow-up surveys administered at 4 weeks, 10 weeks, and 16 weeks post baseline. Data sources to examine efficacy will include a computer-assisted self-interview (self-report measures), pharmacy records, Scene Health app data, and medical records.

Master’s-prepared clinicians (eg, mental health counselors and psychologists) will conduct a comprehensive diagnostic interview using the Mini International Neuropsychiatric Interview (MINI) [60] and the National Institute on Drug Abuse Modified Assist [61]. This will be used to determine a diagnosis and severity of SUD and any co-occurring mental health disorders. Other data collection will include baseline assessment of outcome variables and potential moderators. These self-report questionnaires will be delivered through a REDCap survey. The link will be emailed or texted to the participant based on their preference. Refer to Table 1 for a description of measures and outcomes of interest.

**Table 1 table1:** Overview of phase-wide data collection methods and measures-Harris County, Texas (2021-2025).

Construct			Measure		Study week		Source
**Eligibility**							
	SUD^a^	Substance use and co-occurring mental health diagnoses (Mini International Neuropsychiatric Interview)		0		SUD intake records	
**PrEP knowledge and attitudes (based on barriers identified in aim 1)**							
	PrEP^b^ knowledge	PrEP knowledge questionnaire [62]		0, 4, 10, 16		REDCap^c^ survey	
	PrEP attitudes	PrEP Attitudes Measure [63]		0, 4, 10, 16		REDCap survey	
	PrEP stigma	PrEP Anticipated Stigma Scale (PASS) [64]		0, 4, 10, 16		REDCap survey	
	PrEP adherence self-efficacy	Adherence Starts with Knowledge (ASK-20) [65]		0, 4, 10, 16		REDCap survey	
	HIV risk behaviors	Risk Assessment Battery [66]		0, 4, 10, 16		REDCap survey	
	HIV risk perceptions	Perceived Risk of HIV Scale [67]		0, 4, 10, 16		REDCap survey	
**Initial efficacy (aim 3)**							
	PrEP eligibility	HIV screening, viral hepatitis screening, pregnancy screening, screening for sexually transmitted diseases, and behavioral risk factors		4, 16, 4		Laboratory results Nurse interview	
	PrEP uptake (primary outcome)	PrEP prescription filled and self-reported initial dose of PrEP taken		10, 16		Self-report	
	PrEP adherence (behavioral)	Video-confirmed dose (intervention, daily oral PrEP) Video-confirmed dose (intervention, long-acting injectable [LAI] PrEP, and initial oral cabotegravir) Follow-up injection (intervention LAI) Self-reported dose daily oral PrEP (intervention and standard treatment)		5-16 n/a and 5-16		Scene health reports, study records, study records, and weekly online survey	
	PrEP adherence (laboratory-confirmed)	Tenofovir concentrations (>1000 ng/mL)		16		Laboratory results	

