### Primary Outcome

The primary outcome of interest is PrEP uptake defined as filling the PrEP prescription and taking at least 1 dose of the medication by 2 weeks following their visit with the PrEP provider. The primary outcome will be measured at 12 weeks post completion of the 4-week motivational sessions.

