### Limitation and Strengths

The current study is primarily limited by scale, given that this is a pilot study of HIV-negative Black and Hispanic women living in Houston, Texas, United States, findings may not be generalizable to areas with divergent demographic characteristics. In addition, participants in the control group will provide self-reported data, which may be subject to recall bias. Due to the limited nature of this pilot study mechanism, it is not possible to follow participants for a longer term as would be necessary to draw conclusions about medication adherence. This will be accomplished through a future larger-scale trial of the intervention. In addition, to test the feasibility and acceptability of the Scene Health app components, we required that participants have regular access to a smartphone. The study team’s experience with this population indicates that the vast majority of participants have access to smartphones. However, this can change on an individual bases as participants have difficulties with paying bills, lose phones, etc. The study team will monitor participants’ access as 1 of the aspects of feasibility for this type of intervention to be further explored in a future implementation study. Finally, participants must speak English to meet eligibility requirements, thus potentially limiting the generalizability of findings for Hispanic women who may only speak Spanish.

Despite these limitations, this study has several strengths. First, there are limited studies specifically focused on developing effective behavioral interventions for women with SUD. Second, tailoring the intervention with the use of videos and content representative of women of color has the potential to engage this population more effectively in care than existing interventions. Third, the intervention uses an app that can help support PrEP adherence by providing information, motivation, and behavioral skills necessary to increase the likelihood of starting and staying on PrEP.

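### The sources given for the primary outcome conflict and are not stated to be the same in both arms, which leaves room for differential ascertainment of PrEP uptake

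*Protocol article*

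**What the plan says.** All places are in the protocol article.

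- **Primary Outcome** defines uptake as "filling the PrEP prescription and taking at least 1 dose of the medication by 2 weeks following their visit with the PrEP provider". It therefore has two components, a fill and a first dose. Hypothesis 3a, in Statistical Analysis, is worded on the fill alone.
- **Table 1, Initial efficacy (aim 3)** has one row for this outcome, "PrEP prescription filled and self-reported initial dose of PrEP taken", assessed at weeks 10 and 16. The source column says self-report and makes no distinction by arm.
- **Data Collection** names the efficacy sources as a computer-assisted self-interview plus "pharmacy records, Scene Health app data, and medical records". No efficacy row of Table 1 names pharmacy records.
- **Medication Adherence Monitoring** (intervention arm) asks women to show receipt of the medication by video in the app and then to upload dose videos. Women who have not filled within 2 weeks are booked for another visit.
- **Monetary Incentives, control arm**: "Standard treatment participants will not have access to the Scene Health app and will be asked to respond to a daily yes or no question" in REDCap. Apart from the session payments, the incentives are the same as in the intervention arm.
- **Control Arm**: the referral site tells the research team, with the participant's consent, about attendance and whether a prescription was given. Fill and first dose are not mentioned.
- **Limitation and Strengths** concedes that "participants in the control group will provide self-reported data, which may be subject to recall bias".

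**The concern.** The fill can be established in at least three ways in this article: self-report, pharmacy records, or proof supplied by the participant. The article does not say which one counts. The best evidence is also unequal. In the intervention arm the prescriber sits in the study clinic, unfilled prescriptions are followed up, and receipt and doses are filmed. In the control arm the referral site's report stops at the prescription.

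Participants cannot be blinded, because one arm receives counselling sessions and an app and the other a referral. If whoever codes the outcome draws on whatever evidence is to hand, the two arms will be classified with different accuracy. Control fills that are missed would inflate the apparent effect, and control fills that are over-reported would shrink it. This is the primary comparison, and a later, larger trial is planned to follow this pilot.

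**Working it through.** **1. The sources side by side**

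| Component | Table 1 | Data Collection | Further evidence, intervention | Further evidence, control |
|---|---|---|---|---|
| Fill | Self-report | Pharmacy records listed, not assigned | Receipt video in app | Proof by an undescribed route; site reports prescription only |
| First dose | Self-report | Self-interview, app data | Dose videos | Daily yes/no item in REDCap |

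For the fill, the Table 1 source and the Data Collection list do not agree, and the further evidence differs by arm.

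**2. Do controls also supply proof of fill?** The incentive totals answer this.

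- Intervention, daily oral PrEP: 25 (baseline) + 4 × 10 (sessions) + 25 (first nurse visit) + 10 (proof of fill) + 84 × 1 (12 weeks of daily uploads) + 25 + 25 (two interim data collections) + 25 (90-day visit) + 50 (week 16) = US $309, as stated.
- Control: 309 − 40 = US $269, as stated. Without the US $10 for proof of fill it would be 259.

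So the control total includes payment for proof of fill. The only route the article describes for such proof is the app, which controls do not have.

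**3. What differential ascertainment could do**

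From the document: 60 women, α = 0.05. Assumed, because the article does not state them: 30 per arm, a two-sided pooled z test, and all uptake and error rates. Rejection rates come from exact enumeration of the two binomials, except where noted.

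*Missed control fills.* Observed control rate = p(1 − g), where p is true uptake and g the share missed. With p = 40% in both arms:

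| g | Observed control | Spurious difference | Rejection rate |
|---|---|---|---|
| 0 | 40% | 0 | 4.9% |
| 10% | 0.40 × 0.90 = 36% | +4 points | 5.9% |
| 25% | 0.40 × 0.75 = 30% | +10 points | 12.3% |
| 50% | 0.40 × 0.50 = 20% | +20 points | 39.2% |

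Over p = 20% to 50% and g = 10% to 30%, the spurious difference is +2 to +15 points. Rejection in favour of the intervention rises from about 2.5% to between 3.8% and 21.6%.

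*Over-reported control uptake.* Observed control rate = p + (1 − p)f, where f is the share of control non-initiators counted as uptake. With no true difference, over p = 20% to 50% and f = 10% to 30%, the spurious difference is −5 to −24 points, and rejection in either direction is 6.9% to 51.5%.

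With a true effect of 20% versus 50%, power is 69.2%. If f = 10% in the control arm only, controls show 0.20 + 0.80 × 0.10 = 28% and power is 41.4%. If f = 10% in both arms, the intervention arm shows 0.50 + 0.50 × 0.10 = 55%, the difference is 27 points, and power is 56.7% (normal approximation). The same error in both arms costs less than the same error in one arm.

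**The case against.** A reader might infer that uptake is decided by app video in the intervention arm and by bare self-report in the control arm. The documents do not support that.

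- The Table 1 row for uptake has no arm split. The adherence row below it does label measures by arm, and it is there that video-confirmed doses appear. No section says that video decides uptake; it is described as adherence monitoring and as a trigger for incentives.
- Controls are not shown to be without proof. The US $269 total implies that proof of fill is collected.
- Control information is not confined to weeks 10 and 16. The daily REDCap question means that a control who starts PrEP and later drops out can leave a record.
- The wording of the row attaches self-report to the dose. Together with Data Collection, it can be read as pharmacy record for fill and self-report for dose in both arms, with a shortened source column. That is close to the remedy below.
- This is a pilot, reliance on control self-report is disclosed, and every rate in the illustration is assumed.

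Most of this stands, and it limits the point to a conflict between sources. It does not remove the conflict. The source column names self-report only, pharmacy records are assigned to nothing, and the control route for proof of fill is not given. The favourable reading is possible, but a reader has to construct it.

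**Conclusion.** The point holds as an inconsistency about how the primary outcome is ascertained, one that leaves room for different accuracy in the two arms. It does not show that ascertainment does differ.

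Neither the direction nor the size of any bias can be determined from the documents. Under the assumed rates the effect runs from slight (rejection 5.9% against 4.9% when 10% of control fills are missed at 40% uptake) to serious (39.2% when half are missed), and over-reporting by controls would act the other way. These figures rest on 30 women per arm, a two-sided test, and uptake and error rates that the article does not give.

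This should be fixed rather than treated as a fatal fault; confidence is moderate.

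**What to change.** Change the source in the Table 1 uptake row so that each component has one named source, the same in both arms:

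- **Fill**: pharmacy or dispensing-clinic records, with a release obtained from all women and the same extraction rules whichever arm the record belongs to.
- **First dose**: the same REDCap item, asked at weeks 10 and 16 in both arms.
- **App video**: supporting evidence only, never used to credit uptake in one arm.

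The control arm text should also say how proof of fill is submitted for the US $10 payment.

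The cost is release wording and record requests for about 60 women, from a source the article already lists. The downside is some administrative effort. If outcome data are not yet locked, records can still be requested for women already enrolled, with their release.

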**Feasibility measures (aim 3)**							
	Enrollment rate	Proportion screened who are eligible Proportion eligible who consent		—^d^		Study records	
	Session attendance	Proportion of motivational enhancement sessions attended		—		Study records	
	Use of Scene Health app	Proportion of medication adherence videos uploaded		—		Scene Health reports	
	Study retention	Proportion of participants who remain in the study at 12-week follow-up		—		Study records	
**Acceptability measures (aim 3)**							
	Client satisfaction	Client satisfaction questionnaire		4, 16		REDCap survey	
**Other covariates**							
	Substance use severity	NIDA-Modified Alcohol, Smoking, and Substance Involvement Screening Test [68]		0, 4, 10, 16		REDCap survey	
	Alcohol	Alcohol Use Disorders Identification Test [69]		0, 4, 10, 16		REDCap survey	
	Health literacy	Calgary Charter on Health Literacy Scale [70]		0		REDCap survey	
	Medical mistrust	Group Based Medical Mistrust Scale [71]		0, 4, 10, 16		REDCap survey	
	Trauma	Life Events Checklist/PTSD^e^ Checklist for *DSM-5*^f^ [72,73]		0, 4, 10, 16		REDCap survey	
	Depression	Patient Health Questionnaire-9 [74]		0, 4, 10, 16		REDCap survey	
	SUD treatment attendance	Number of substance use disorder therapy sessions attended		16		Study records	

^a^SUD: Substance use disorder.

^b^PrEP: pre-exposure prophylaxis.

^c^REDCap: Research Electronic Data Capture.

^d^Not applicable.

^e^PTSD: posttraumatic stress disorder.

^f^*DSM-5: Diagnostic and Statistical Manual of Mental Disorders* (Fifth Edition).

